### Eligibility criteria {10}

#### Participants

##### Inclusion criteria

According to the Kidney Disease: Improving Global Outcomes (KDIGO) guidelines, CKD refers to the abnormalities in the kidney structure or function or an estimated glomerular filtration rate (eGFR) of < 60 ml/min/1.73 m^2^ that persists for 3 months with or without kidney damage. The GFR was obtained by calculating the CKD-EPI using the following Cystatin C formula: eGFR=169 × Scr^-0.608^ × CysC^−0.63^ × Age^−0.157^ × (0.83 if female).Patients diagnosed with CKD stages 3–5 (non-dialysis dependent) aged 30–65 years (including those aged 30 and 65 years).Sex and ethnicity restrictions were not imposed.Patients without atherosclerosis in the common carotid artery as observed on the vascular ultrasound examination and no history of atherosclerosis in the carotid artery.An informed consent form from participants is required (Supplementary document).

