**Secondary**		
The combined cardiovascular events	Incidence	**36** months
All-cause mortality	Incidence	**36** months
eGFR decreased by 50%	the proportion of eGFR decreased by 50%	**36** months
Safety outcomes	Numbers	**36** months

Carotid ultrasonography will be used to screen for atherosclerosis. The bilateral carotid arteries will be analyzed by color Doppler ultrasound at a frequency of 10 MHz using a linear array transducer (Model Vinno 70; VINNO Technology (Suzhou) Co., Ltd., China) by an experienced sonographer. A smooth carotid artery is considered normal. An atherosclerotic plaque is defined as a focal structure encroaching into the arterial lumen by at least 0.5 mm or 50% of the surrounding intima-media thickness (IMT) value or with a thickness of > 1.5 mm, as measured from the media-adventitia interface to the intima-lumen interface [21]. Both atherosclerotic plaques and IMT are indicators of carotid atherosclerosis. The carotid ultrasonography will be performed at 6, 12, 24, and 36 months to identify the status of carotid atherosclerosis.

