#### Secondary outcomes

The combinations of cardiovascular events are as follows:
Acute ST-induced myocardial infarction: Evidence of myocardial ischemia, one of the following factors, and the rise or fall of the biochemical marker values (preferably cardiac troponin) with at least one value above the 99th percentile upper reference limit: (A) symptoms of ischemia, (B) new or presumed new significant ST-segment–T wave (ST–T) changes or new left bundle branch block, (C) development of pathological Q waves in the electrogram (ECG), (D) imaging evidence of new loss of viable myocardium or new regional wall motion abnormality, and (E) identification of an intracoronary thrombus on angiography or autopsy.Other acute coronary syndromes: In patients experiencing ischemic symptoms (pain at rest, shortness of breath, press-like discomfort, or progressive exacerbation of the above symptoms), rest or use of nitrates will not relieve these symptoms. On ECG, a transient or persistent ST-segment offset of 0.1 mV or above in one or more leads is usually observed.Congestive heart failure requiring hospitalization: Normal venous reflux is a clinical syndrome characterized by tissue hypoperfusion and pulmonary or systemic circulatory congestion marked by a decrease in cardiac output and an increase in ventricular filling pressure due to the presence of a primary cardiac damage and cardiac insufficiency.Severe arrhythmias: cardiac arrest and resuscitation, ventricular fibrillation, persistent ventricular tachycardia, paroxysmal ventricular tachycardia, primary atrial fibrillation or atrial flutter, severe sinus bradycardia, and complete atrioventricular block after a percutaneous coronary intervention or coronary artery bypass grafting. The occurrence of combined cardiovascular events will be recorded in every visit within the period of 3 years.All-cause mortality. The mortality from any other cause will be registered. These events will be collated during the 3-year follow-up.eGFR decreased by 50%. The eGFR will be calculated at every visit. When the trial is completed, patients in both groups whose eGFR decreased by 50% will be judged as experiencing a renal event.

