### Statistical analysis

#### Statistical methods for primary and secondary outcomes {20a}

For the primary outcome, the chi-square test will be performed to compare the occurrence rate of atherosclerosis at 1, 2, and 3 years of follow-up between the aspirin group and the placebo group. For the secondary outcome, the chi-square test will be performed to compare the combined cardiovascular events and all-cause mortality at 1, 2, and 3 years of follow-up between the aspirin group and the placebo group. Then, the decrease in eGFR will be computed using the value measured at the last follow-up minus the value measured at baseline; patients with a 50% decline in eGFR will be treated as patients who experienced an eGFR reduction of 50%. Similarly, the proportion of patients with an eGFR reduction of 50% between the aspirin group and the placebo group will be compared using the chi-square test. If the previous comparison did not reach a significant difference, the magnitude of decrease in eGFR between the two groups would be compared using two independent sample *t* tests or the Mann-Whitney *U* tests. In addition, multivariate competing-risk regression models will be used to assess the independent effect of treatments adjusted for age, sex, diabetes, serum lipid profiles, and phosphorus.

All statistical analyses will be performed using the SPSS software version 21.0 (IBM Corp., Armonk, NY, USA), and general data will be expressed as mean ± standard deviation. The variables with normal distribution and variance will be compared. One-way analysis of variance will be used for comparisons within groups. The SNK test will be used for multiple comparisons between groups. Pearson’s correlation analysis will be used for analyzing the correlation between variables. A nonparametric test will be used to analyze variables that do not meet the parameter test conditions. The Kruskal-Wallis *H* test or Mann-Whitney *U* test will be used for data comparison. Spearman’s correlation analysis will be used for correlation analysis. The chi-square test will be used for comparison. A *p* value of < 0.05 will be considered significant. A nonparametric test for multiple comparisons will be corrected using the Bonferroni method, *p* < 0.008, statistically significant safety analysis.

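### The eGFR 'decrease' is written with the subtraction reversed and without the baseline denominator that the 50% decline needs

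*Protocol article*

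**What the plan says.** All passages are in the protocol article.

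- **Statistical methods for primary and secondary outcomes {20a}** gives the only derivation: "the decrease in eGFR will be computed using the value measured at the last follow-up minus the value measured at baseline". After a semicolon it adds that "patients with a 50% decline in eGFR will be treated as patients who experienced an eGFR reduction of 50" per cent. The proportions are compared by chi-square test.
- **The same section** uses the difference again. If the proportions do not differ significantly, "the magnitude of decrease in eGFR between the two groups would be compared using two independent sample" t tests or Mann-Whitney U tests.
- **Secondary outcomes** says that, at trial completion, "patients in both groups whose eGFR decreased by 50% will be judged as experiencing a renal event".
- **Table 1** gives the metric as "the proportion of eGFR decreased by 50" per cent, at 36 months.
- **Inclusion criteria** admit "Patients diagnosed with CKD stages 3–5 (non-dialysis dependent) aged 30–65 years", so baseline eGFR lies below 60 and varies widely.

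No section writes a percentage-change formula or names baseline as the divisor.

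**The concern.** A decrease is the starting value minus the later value. The written rule subtracts the other way, so the variable called a decrease is negative for patients who get worse and positive for patients who improve. The difference is also on the absolute scale, while the outcome it introduces is a percentage.

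Two things are at stake. One is how the renal result is read. The Discussion cites studies suggesting that low-dose aspirin may increase CKD progression, so the direction of this estimate is of safety interest. A table of mean 'decrease' built as written would give the arm that loses more function the lower number. The other is efficiency. The continuous comparison is an unadjusted test on raw change in a population whose starting values differ greatly, although baseline eGFR is available.

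**Working it through.** There is no stated figure to reproduce: no sample size, power or alpha value depends on this rule. The check applies the rule to example records. The eGFR values are assumptions, with baselines inside the entry range.

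**Formulas**
- As written: D = last - baseline.
- Percentage decline: P = 100 x (baseline - last) / baseline.

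| Baseline | Last | D as written | P |
|---|---|---|---|
| 40 | 18 | -22 | 100 x 22/40 = 55% |
| 50 | 25 | -25 | 100 x 25/50 = 50% |
| 20 | 10 | -10 | 100 x 10/20 = 50% |
| 50 | 60 | +10 | 100 x (-10)/50 = -20% |
| 58 | 38 | -20 | 100 x 20/58 = 34% |
| 24 | 10 | -14 | 100 x 14/24 = 58% |

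**Sign.** Every patient who loses function has a negative D, and the patient who improves has a positive one. The label and the formula disagree.

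**Denominator.** Rows two and three are the same 50% fall but give D of -25 and -10, so D alone does not identify the event. Dividing D by baseline gives -50% in both rows. A change of sign and a divisor are therefore all that is missing.

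**Scale.** Row five has the larger absolute fall (20 against 14) but is well short of 50%, while row six exceeds it. The absolute comparison and the 50% endpoint can rank patients differently.

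**Effect of the sign on the tests.** Replacing D by -D in both arms changes the t statistic only in sign. It changes the Mann-Whitney statistic from U to n1 x n2 - U, which is equally far from its null mean. Two-sided p values are unchanged. A numerical check used 277 simulated patients per arm, with changes drawn from normal distributions with assumed means -8 and -6 and SD 10. It gave 1.17e-05 for the t test with either sign and 1.02e-05 for Mann-Whitney with either sign.

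**Efficiency.** A t test on D amounts to a regression of follow-up eGFR on arm with the coefficient of baseline fixed at 1. ANCOVA estimates that coefficient, so in samples of this size its residual variance is no larger apart from the one degree of freedom used, and it is smaller whenever the true slope differs from 1. The documents give no correlation between baseline and follow-up eGFR, so the gain cannot be put as a figure. The competing-risk models named later in {20a} do not list baseline eGFR among their covariates, so they do not supply this adjustment.

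**The case against.** The strongest reply is that this is a wording slip. The semicolon separates two clauses, and nothing says that the raw difference is itself the 50% criterion. Secondary outcomes and Table 1 both state the direction of the event. A percentage decline is normally taken relative to the starting value, and baseline is the only reference value named. That stands: a careful analyst would classify patients correctly.

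It is also fair that last minus baseline is an ordinary change score, that absolute eGFR change is a legitimate continuous outcome, and that an unadjusted test of it is valid under randomization. The ANCOVA is therefore a gain in precision and not the repair of an invalid test.

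A further reply is that a condensed article may leave the exact formula to the full protocol. That would excuse silence about the denominator. It does not excuse the subtraction, because the article does print a rule and the rule runs against the name it gives the quantity.

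A reader might infer that the 50% endpoint cannot be computed, or that the reversed sign would make harm test as benefit. The documents support neither. The endpoint follows from the ordinary meaning of the text, and no two-sided test result depends on the sign.

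**Conclusion.** The point holds as an error of definition with limited consequences. The only stated computation for a named secondary endpoint has its sign reversed, and it leaves out the divisor needed for the percentage it introduces. Event status remains derivable, two-sided p values are unaffected, and the primary outcome and sample size are not touched.

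What remains is the risk that the mean 'decrease' is reported with its direction misread, plus avoidable imprecision in the continuous comparison across stages 3–5. The arithmetic on the sign and denominator needs no assumption beyond the example values. How many patients or how much precision would be affected cannot be estimated from the documents, and no figure is claimed.

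**What to change.** Replace the sentence in {20a} with a definition such as: percentage decline = 100 x (baseline eGFR - follow-up eGFR) / baseline eGFR, and a renal event is a percentage decline of 50% or more. Use the same definition in Secondary outcomes and Table 1. This also settles that the threshold means at least 50%, which the text does not say.

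For the continuous comparison, replace the unadjusted t test on the raw difference with ANCOVA of follow-up eGFR on treatment and baseline eGFR, and report the treatment effect with a 95% CI. Analysing both eGFR values on the log scale is an option; the effect is then a ratio, which matches the relative endpoint.

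The cost is a sentence or two in the analysis section. Baseline eGFR is already needed for the planned difference, so there is no new data collection and no change to the sample size. The change should be made before unblinding.

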### Participant timeline {13}

The time schedule of enrollment, intervention assessments, and frequency of visits of all participants are shown in a schematic diagram (see the Research flow chart). The participants will be followed up at 0.5, 1, 2, 3, 4, 5, 6, 12, 24, and 36 months.

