#### Methods in analysis to handle protocol non-adherence and any statistical methods to handle missing data {20c}

For missing data imputation, the last observation carried forward method will be used if the missing data met the following hypothesis: missing completely at random.

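### The eGFR decrease is taken at each patient's last follow-up with no adjustment for time observed, so unequal early exits between arms would bias the comparison

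*Protocol article*

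**What the plan says.** Under Statistical methods for primary and secondary outcomes {20a}, the article defines the change: "the decrease in eGFR will be computed using the value measured at the last follow-up minus the value measured at baseline". The 50% decline status is derived next, and "the proportion of patients with an eGFR reduction of 50% between the aspirin group and the placebo group will be compared" by chi-square. If that test is not significant, "the magnitude of decrease in eGFR between the two groups would be compared using two independent sample" t tests or Mann-Whitney tests. No common visit is named there, and the change is not divided by time on study.

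Four other places bear on the point:

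- Table 1 gives the metric as "the proportion of eGFR decreased by 50" percent, at 36 months. The Secondary outcomes section judges the renal event at the end of the trial.
- The same section says "The eGFR will be calculated at every visit", and the Participant timeline {13} says "The participants will be followed up at 0.5, 1, 2, 3, 4, 5, 6, 12, 24, and 36 months".
- On missing data, section {20c} says "the last observation carried forward method will be used if the missing data met the following hypothesis: missing completely at random". It gives no rule for data that do not meet that condition.
- Section {20a} adds that "multivariate competing-risk regression models will be used to assess the independent effect of treatments adjusted for age, sex, diabetes" and other covariates, without naming the outcome, the event time or the competing event.

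**The concern.** In stage 3–5 CKD, eGFR can be expected to fall with time. A patient last seen at month 3 contributes three months of decline and a completer contributes thirty-six, yet both enter the same test as if they measured the same thing. Seven of the ten follow-up visits lie in the first six months, so the last value of an early leaver may cover only weeks.

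If one arm loses more patients, or loses them sooner, its average fall looks smaller with no drug effect at all. The trial could then report a kidney benefit, or hide a harm, that comes only from follow-up time. The 50% decline outcome is exposed in the same way, because a patient who leaves early has had less time to cross the threshold.

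**Working it through.** **Is there a reading that avoids the problem?** Suppose last follow-up means the month-36 visit, as Table 1 suggests. A patient who left earlier has no value there. LOCF, the only method the plan names, fills it with that patient's last value, so the number is the same. Missingness completely at random does not rescue LOCF here, because carrying a value forward assumes no further decline. The competing-risk model is an addition and is not tied to this comparison.

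**Inputs from the article:** 277 per group and 10% loss to follow-up (Sample size {14}); the ten visits; two-sided 5%. The article gives no rate of eGFR loss, no exit imbalance and no power for this outcome, so there is no figure of its own to reproduce.

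**Assumptions:** no treatment effect; mean loss of 2 or 4 ml/min/1.73 m² per year; between-patient slope SD 3; measurement SD 3; exits unrelated to the rate of fall.

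**Mean time of the last value in early leavers:**

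- Exits spread evenly over the nine visits before month 36: (0.5+1+2+3+4+5+6+12+24)/9 = 57.5/9 = 6.4 months = 0.53 years. Lost exposure is 3 − 0.53 = 2.47 years.
- Exits spread evenly over calendar time, using the last visit attended: 483.25/36 = 13.4 months = 1.12 years. Lost exposure is 1.88 years. The numerator sums each visit month times the number of months until the next visit.

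**False difference** = (difference in exit share) × (annual loss) × (lost exposure).

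**Standard error.** The SD of a completer's change is √((3×3)² + 2×3²) = √99 = 9.95. The SE is 9.95 × √(2/277) = 0.85. Two-sided error is P(|Z + difference/SE| > 1.96).

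| Annual loss | Exits | False difference, even over visits | Error | False difference, calendar time | Error |
|---|---|---|---|---|---|
| 4 | 15% vs 5% | 0.10×4×2.47 = 0.99 | 21% | 0.10×4×1.88 = 0.75 | 14% |
| 2 | 15% vs 5% | 0.10×2×2.47 = 0.49 | 9% | 0.10×2×1.88 = 0.38 | 7% |
| 4 | 12.5% vs 7.5% | 0.05×4×2.47 = 0.49 | 9% | 0.05×4×1.88 = 0.38 | 7% |
| any | equal | 0 | 5% | 0 | 5% |

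Simulations of 277 per arm agree: 0.96 to 0.99 with 21%, and 0.49 with 9%, for exits over visits; 0.72 with 14%, and 0.38 with 7.5%, over calendar time (15% vs 5% in each case).

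**The 50% decline outcome.** This was simulated with further assumptions: baseline mean 35, SD 12; losses of 2, 3 and 5 per year; exits 15% vs 5%, even over visits. The crude chi-square on the last value declared a false benefit in 6%, 9% and 14% of trials, against a nominal 2.5%. At a loss of 3 per year the proportions were 19.0% vs 21.1%. A log-rank test of time to first 50% decline, censored at exit, gave about 2% throughout.

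**Does the remedy work?** A random-slope mixed model gave a mean difference of −0.19 (Monte Carlo SE about 0.10) with 2.5% rejection in one check of 80 trials, and −0.05 (SE 0.11) with 5% rejection in another. These are small runs and support the remedy only roughly.

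**The case against.** Several points on the other side stand.

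- **Standing of the comparison.** The test of magnitude is not a listed outcome. It runs only when the 50% decline test is not significant, in a trial that its own text calls exploratory and a pilot. That limits the weight of the point. It does not remove it, since the listed 50% outcome uses the same last value.
- **Imbalance is assumed.** The article plans 10% loss overall and says nothing about a difference between arms. A modest imbalance at that overall rate does little harm, as the third row of the table shows. A reader might infer that the t test will reject well above 5%; the documents do not support that without an assumed imbalance.
- **Aspirin intolerance.** A reader might infer that intolerance will produce a false kidney benefit for aspirin. The section on discontinuing the intervention {11b} does list intolerance, treatment gaps and withdrawal. But stopping the drug is not leaving follow-up, section {20b} states intention-to-treat, and nothing says that eGFR collection ends when the drug stops. The direction of any bias is open.
- **Visit schedule.** Collection of basic information lists blood specimens only at baseline and 1, 6, 12, 24 and 36 months, which sits badly with eGFR at every visit. On that shorter schedule, exits spread evenly over months 1, 6, 12 and 24 average 10.75 months. The first row then becomes 0.10×4×(3 − 0.90) = 0.84, inside the range shown.
- **Choice of remedy.** Comparing change at month 36 among those observed also removed the bias in simulation (−0.04 to 0.00), with exits unrelated to eGFR. The mixed model is therefore not the only repair. Its advantages are that it uses every value and needs only exits missing at random.

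**Conclusion.** The point holds in a conditional form. As written, the eGFR change mixes time observed with treatment effect, and neither the 36-month time point nor the LOCF rule prevents that. Bias between arms needs exits that differ in number or timing. Its stated direction also assumes that eGFR falls over time and that exits are not driven by how fast it falls, so it is not inevitable.

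At 15% versus 5% exits the false difference is about 0.4 to 1.0 ml/min/1.73 m², with two-sided error of about 7% to 21% depending on rate of loss and exit timing. With equal exits there is no false difference, but the mean decline is understated in both arms. The rates, SDs and exit shares are assumptions, not figures from the article. The primary outcome and the sample size are unaffected. It is worth correcting because the correction is cheap and also covers a listed secondary outcome.

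**What to change.** In section {20a}, replace the last-minus-baseline t or Mann-Whitney test by a linear mixed model of all scheduled eGFR values. Use baseline eGFR as the first measurement, fixed effects for time, arm and arm-by-time, and random intercept and slope. Report the arm difference in annual slope or in model-estimated change at month 36. State in {20c} that LOCF is not used for eGFR.

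Analyse the 50% decline as time to first 50% decline, censored at exit, in place of the crude chi-square on the last value. Align the wording in Table 1 and Secondary outcomes, which now judge it at the end of the trial. Make these changes before unblinding.

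The cost is wording only, with eGFR values that the plan already has calculated at visits; the visit and specimen schedules should be made to agree. The downside is that the model assumes a roughly linear course and exits missing at random.

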### Sample size {14}

#### Sample size estimation

The sample was calculated as follows: $$ n=\frac{{\left({z}_{\alpha}\sqrt{2\overline{pq}}+{z}_{\beta}\sqrt{p1q1+p0q0}\right)}^2}{{\left(p1-p0\right)}^2} $$

In this study, p0 and p1 represent the estimated exposure rates of the control group and the experimental group, respectively, while *Z*_α_ and *Z*_β_ indicate the standard positive distribution boundaries. In the table, when *α* or *β* is equal to 0.05, its value is 1.96; when *α* or *β* is equal to 0.01, its value is 2.58. In this study, the incidence of p0 is above 40% [8]. After the intervention, p1 is expected to decrease by 15% compared with p0 (p1 = 25%). Let *α* = 0.05 (both sides), and *β* = 0.10. The calculated minimum sample size is 251; if 10% of the cases were lost to follow-up, the calculated sample size would be 277 for each group, and approximately 554 patients will be included in the trial.

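### The eGFR change is tested only if the 50%-decline test fails, with no correction for the pair, and the renal event rests on eGFR alone, so some patients reaching dialysis or transplant count as event-free.

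*Protocol article*

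**What the plan says.** Table 1 lists one kidney outcome, the proportion of patients whose eGFR fell by 50%, at 36 months. Under Secondary outcomes, eGFR is calculated at every visit and, once the trial is complete, "patients in both groups whose eGFR decreased by 50% will be judged as experiencing a renal event".

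Statistical methods for primary and secondary outcomes {20a} gives the analysis. The decrease is "computed using the value measured at the last follow-up minus the value measured at baseline", and the proportions with a 50% decline are compared by chi-square. A second step follows: "If the previous comparison did not reach a significant difference, the magnitude of decrease in eGFR between the two groups would be compared", by t test or Mann-Whitney U test. The general threshold is that a p "value of < 0.05 will be considered significant". The only multiplicity rule is a Bonferroni limit of p < 0.008, attached to nonparametric multiple comparisons and the safety analysis. The same section plans a multivariable competing-risk regression but names neither its endpoint nor its competing event.

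Eligibility is CKD stages 3–5, not dialysis dependent, and kidney transplant patients are excluded at entry. The article does not say how dialysis or transplant after randomization is counted.

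**The concern.** There are two faults in stated rules.

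First, the continuous eGFR comparison is run only after the event comparison has failed, so the kidney question gets a second chance at the full 0.05. It is also reported selectively: when the event test is significant, the reader never sees whether the continuous change agrees with it.

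Second, the event depends only on a last eGFR set against baseline. In a stage 3–5 population followed for 36 months, starting dialysis is foreseeable. A patient with a low baseline can reach it before eGFR has halved. After dialysis or transplant, a later eGFR no longer reflects the patient's own kidney function. After a transplant it may even look like improvement.

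The Discussion cites studies suggesting that low-dose aspirin may increase CKD progression. The kidney outcome therefore bears on safety, and both a spurious finding and uncounted kidney failure would matter.

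**Working it through.** **Inputs from the article.** Two-sided 0.05 per test ({20a}; Sample size estimation: "Let *α* = 0.05 (both sides), and *β* = 0.10"). Group size 251 before allowance for loss (Sample size estimation). Visits at 0.5, 1, 2, 3, 4, 5, 6, 12, 24 and 36 months (Participant timeline). The article states no error rate for the two-step kidney rule, so there is no such figure to reproduce. The 251 serves here only as a group size. The stated formula returns it with β = 0.05, and 203 with the stated β = 0.10; that is a separate matter and does not affect this point.

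**Step 1: what the rule amounts to.** Let A be a significant chi-square and B a significant continuous test. A kidney effect is claimed if A occurs, or if A does not occur and B does:

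P(A) + P(not A and B) = P(A or B)

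So the rule has the same error rate as running both tests every time and accepting either. Deleting the condition alone would not bring it back to 5%.

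**Step 2: independence.** 1 − (1 − 0.05)² = 1 − 0.9025 = 0.0975.

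**Step 3: correlated tests.** Both tests use the same eGFR values. For bivariate normal statistics:

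| Correlation | P(A or B) |
|---|---|
| 0.3 | 0.0951 |
| 0.5 | 0.0906 |
| 0.7 | 0.0835 |
| 0.9 | 0.0705 |

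**Step 4: simulation with no treatment effect.** The article gives no eGFR distribution, so one is assumed: baseline uniform from 8 to 59, and relative change normal with mean −10% to −30% and SD 17% to 25%. There were 251 patients per group and 20,000 trials per scenario, with chi-square on a fall of at least 50%, then a t test on relative or absolute change. Across ten scenarios:

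- 50%-decline rate: 0.9% to 21.2%
- Correlation of event with change (absolute value): 0.23 to 0.71
- Chi-square alone: 4.4% to 5.2%; t test alone: 4.8% to 5.2%
- Either significant: 8.3% to 9.3%, which is 0.0826/0.05 = 1.65 to 0.0934/0.05 = 1.87 times nominal

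**Step 5: could the p < 0.008 rule rescue it?** If it governed a Mann-Whitney second step, the independence figure would be 1 − 0.95 × 0.992 = 0.0576. The text does not tie it to that step, and it would not cover the t test.

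**Step 6: event definition.** An event needs a last value of at most half the baseline. From an illustrative baseline of 14 that means 7 or below. A fall to 8 is (14 − 8)/14 = 42.9%, so a patient who starts dialysis at 8 is scored as having no event.

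**Step 7: timing.** After month 6 the visits are at 12, 24 and 36 months. A patient who leaves at month 11 has a last value from month 6, against the 36-month time point in Table 1. Section {20c} allows last observation carried forward if data are missing completely at random, which would keep that value.

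**The case against.** **The error rate.** Table 1 names one renal outcome, and its chi-square test alone holds about 5%. This is a secondary outcome in a trial called exploratory (Trial design) and a pilot (Discussion), and the second test is disclosed in advance. That limits the severity, and the inflation applies only if a positive second test is presented as a kidney effect. But nothing in {20a} labels that test supportive, and running it only after a null result invites exactly that reading. A reader might infer that the error rate doubles. The documents do not support that: 9.75% needs independent tests, and these share their data.

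**Dialysis and transplant.** Handling rules may sit in a full protocol or analysis plan that is not shown, and a composite endpoint can be called a preference. However, the definition is stated in Table 1, Secondary outcomes and {20a}, each time by eGFR alone. A reader might infer that the outcome misses kidney failure altogether. It does not: a patient whose last eGFR has halved before dialysis is counted. The gap is failure without a recorded halving, or with a later eGFR altered by treatment. The article gives no figure for how many patients that is.

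**Timing.** A reader might infer that {20a} deliberately pools 6-month and 36-month values. The last follow-up can equally be read as the month-36 visit, given Table 1 and the statement that events are judged at trial completion. The mixing arises for dropouts only.

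**The planned competing-risk model.** It could help, but no endpoint or competing event is named for it, and it is added to the two-step rule without replacing it.

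**Conclusion.** The point holds for a secondary outcome. Under the two-step rule, the chance of a false kidney finding is about 8–9% if either result is accepted, and 9.75% if the tests were independent. The range rests on assumed eGFR distributions, but every simulated scenario exceeded 8%. The conditional trigger adds no error beyond accepting either of two tests; its particular harm is that the continuous result is shown only when it can rescue a null one.

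The renal event as printed scores as event-free any patient who reaches dialysis or transplant without a recorded 50% fall, and may misclassify those whose later eGFR is altered by either. For dropouts the last value may fall well short of 36 months. The size of these two effects cannot be derived from the article.

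**What to change.** 1. Delete the condition that makes the continuous comparison depend on a non-significant event test.
2. Name the renal-event comparison as the single renal test at 0.05. This step, not the deletion, restores the 5% rate. Splitting alpha as 0.025 + 0.025 would also work (1 − 0.975² = 0.0494 if independent), but one designated test is simpler.
3. Always report the eGFR change with a 95% CI, labelled supportive, preferably from a mixed model over all visits with values after dialysis or transplant excluded.
4. Count the start of maintenance dialysis or a kidney transplant as a renal event alongside a 50% eGFR decline. Analyse it over follow-up with the competing-risk model already planned, naming death as the competing event. State that this model supplies the designated test, so that a chi-square on the same event does not become a second one.
5. Do not require the decline to be sustained. A fall first seen at month 36 could not be confirmed without a visit beyond the schedule.

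The cost is one date field for dialysis or transplant and a small change to a secondary outcome definition, which needs an amendment. eGFR is already calculated at every visit. Without a confirmation rule, some transient falls will count as events.
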